**Fig. 1 Fig1:**
[figure not shown]
Study set-up. (**A**) Ninety participants will be randomized into six groups of 15 subjects each, receiving either the baseline dose of estradiol (group A), the baseline dose of estradiol and progesterone 200 mg daily (**B**), the baseline dose of estradiol and progesterone 400 mg daily (**C**), twice the baseline dose of estradiol (**D**), twice the baseline dose of estradiol and progesterone 200 mg daily (**E**), or twice the baseline dose of estradiol and progesterone 400 mg daily (**F**). (**B**) The study will include 12 months of follow-up after the start of the intervention. Visits are scheduled at baseline, after 3, 6 and 12 months

The established feminizing hormone therapy for transgender women after vaginoplasty or orchiectomy consists of estradiol, prescribed as tablets, patches, gel or spray. The baseline dose of estradiol (groups A, B, C) is defined as oral estradiol valerate (Progynova®), or estradiol hemihydrate tablets (generic, Estradiol Sandoz®, Estrofem®, Zumenon®), or transdermal estradiol patches (Systen®, Sandoz®), estradiol gel (Oestrogel®) or spray (Lenzetto®) resulting in serum estradiol concentrations of 200–400 pmol/L, which are the current local reference ranges. Twice the baseline dose of estradiol (groups D, E, F) is defined as doubling of the estradiol dose of the participant at study entry in order to achieve and maintain serum estradiol concentrations of 400–800 pmol/L. These higher concentrations can be considered safe as these are within the reference ranges stated in the international guideline for hormone treatment of gender dysphoria [2].

Two doses of micronized progesterone are tested in order to investigate a potential dose-response effect. If a dose-response relation is established, this would support a biological effect of the treatment. The duration of the study will be approximately three years in total and will include 12 months of patient follow-up after the start of the intervention (Fig. 1B). Visits are scheduled at baseline, after 3, 6 and 12 months. The study protocol is in line with the Standard Protocol Items: Recommendation for Interventional Trials (SPIRIT) guidelines (Fig. 2).

**Fig. 2 Fig2:**
[figure not shown]
Spirit figure of the trial

### Main study parameter/endpoints

The main study end point is breast volume change over the duration of this study. For this purpose, 3D breast images and breast-chest circumference differences are measured (centimeters). 3D imaging of the breasts is carried out using an Artec Leo 3D (Artec 3D, Luxembourg, Luxembourg) scanner in order to determine breast volume. The Artec LEO is a wireless vertical cavity surface-emitting laser scanner (VCSEL) and an improved and more accurate version of the Artec Eva 3D scanner. Previous research has shown that the Artec Eva 3D scanner provides accurate, valid and reliable 3D scans [19, 20]. The Artec LEO can be used with Artec Studio software version 15.1.2.60. All 3D scan files are analyzed in GOM-inspect (GOM, Braunschweig, Germany) and Meshmixer (Autodesk Research, San Francisco, U.S.A.) for breast volume estimation in cubic centimeters (cc). Bra cup sizes will be calculated from breast-chest circumference differences and from the 3D images.

After inclusion, we obtain a complete history (including current or previous illnesses, medication, smoking, alcohol use, family history, previous use of progesterone and cyproterone acetate). At baseline and during follow-up, the following patient characteristics will be recorded: age, height, weight, BMI, blood pressure, alcohol use, smoking, type of estradiol use and breast volume. At the start of the study and after six and twelve months, venous blood samples are obtained and analyzed for determination of concentrations of 17-beta-estradiol, progesterone, luteinizing hormone (LH), follicle-stimulating hormone (FSH), prolactin, sex hormone-binding globulin (SHBG), as well as alkaline phosphatase (APH), gamma-glutamyltransferase (gamma-GT), alanine-aminotransferase (ALAT) and aspartate-aminotransferase (ASAT), low-density lipoprotein (LDL) and HDL cholesterol and triglyceride levels. Estradiol concentrations will be measured using liquid chromatography followed by mass spectrometry. Progesterone, LH, FSH, prolactin and SBHG will be measured using immunoassays.

Satisfaction is assessed at the start of the intervention and during the follow-up visits by three online questionnaires: the Rosenberg self-esteem scale [21], the Breast Satisfaction Rating Scale (BSRS) and a non-validated satisfaction questionnaire about various aspects of the breasts [5]. Satisfaction is measured with regard to several aspects such as symmetry of the breast, the breast volume, and size and shape of the nipple. In addition, adverse and serious adverse effects are recorded. Further, mood and sleep quality will be assessed using the Perceived stress scale, Inventory of Depressive Symptomatology, self-report (IDS-SR) and Pittsburgh Sleep Quality Index (PSQI) questionnaires. Levels of experienced sexual pleasure will be assessed using the Amsterdam Sexual Pleasure Index (ASPI) [22].

### Statistical analysis

All analyses will be performed using the most recent version of STATA. Baseline data will presented as mean with SD for normally distributed data, and median with interquartile ranges for nonnormally distributed data. Data on tobacco use and alcohol use will be presented as percentage of users. The analyses will be blinded with regard to the treatment regimen for the researcher performing the data analyses. Estradiol use will be coded as 0 (normal dosage) or 1 (double dosage), and progesterone will be coded as 0 (no use), 1 (200 mg), or 2 (400 mg). Thereafter, linear mixed model analyses with measurements clustered within participants will be performed, with breast volume as continuous outcome variable and time with set time points at 0, 3, 6, and 12 months as determinants [23]. Estradiol and progesterone use will be analyzed separately and as interaction terms. By performing analyses this way, the separate effects of estradiol and progesterone can be assessed, as well as the effects of the various treatment combinations. Breast size and volume measurements will be recorded in cc. All data are presented as mean change in cc with 95% confidence intervals. Individual-level outliers will be identified with a standardized residual cut-off point of ± 5 [24]. Non-normally distributed data will be log-transformed before mixed-model analyses. The mixed model analysis method can be used and adapted to compensate for missing values and assess potential effect modifying factors. Analyses will be stratified to treatment regimen, age, weight change and serum hormone levels. Age will be analyzed in quartiles and weight change will be assessed in 10 kg groups. Analyses for serum hormone levels will be stratified in quartiles. Satisfaction, mood, sleep, and sexual desire will be recorded as categorical variables. Sexual pleasure will be assessed using a continuous scale of the ASPI score. To analyze the relationship between satisfaction of different aspects of the breasts and breast volume, mixed model analyses will be performed. Treatment regimens, hormone levels and breast volume changes will be assessed as covariates. Side effects and adverse events will be recorded as percentages and analyzed using Fisher’s exact testing.

We considered an average increase of 30% of breast volume – corresponding to one bra cup size increase – as a clinically relevant outcome after one year of study treatment. From previous studies, it is known that the ratio of two consecutive breast volume measurements is 1.08 with a standard deviation of 0.27 [5]. Using a power simulation model (STATA, factorialsim), in which the increase of the estradiol dose is treatment A and addition of progesterone is treatment B in a factorial design of six groups of 15 subjects, at a set alpha of 0.05 the simulated power of A is estimated at 0.95 and the power of B at 0.94.

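### As worded, the primary mixed model does not estimate the stated endpoint: it models volume level over four visits and ties no treatment term to time, while the target is the change after one year

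*Protocol article*

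**What the plan says.** All references are to the protocol article.

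- **Endpoint** (Main study parameter/endpoints): "The main study end point is breast volume change over the duration of this study".
- **Target effect** (Statistical analysis, sample-size paragraph): a 30% average increase in breast volume is taken "as a clinically relevant outcome after one year of study treatment".
- **Visits** (Fig. 1 legend): "Visits are scheduled at baseline, after 3, 6 and 12 months".
- **Model** (Statistical analysis): a mixed model for the repeated measurements on each person, specified "with breast volume as continuous outcome variable and time with set time points at 0, 3, 6, and 12 months as determinants". The outcome is the volume itself, and month 0 is one of its time points.
- **Treatment terms** (same section): estradiol is coded 0/1 and progesterone 0/1/2. "Estradiol and progesterone use will be analyzed separately and as interaction terms". The stated purpose is that "the separate effects of estradiol and progesterone can be assessed, as well as the effects of the various treatment combinations".
- **Reporting** (same section): "All data are presented as mean change in cc with 95% confidence intervals".

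The section does not say which model coefficient yields that change.

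**The concern.** The named terms are time, estradiol, progesterone and an interaction whose only explained role is to separate dose combinations. With the volume level as outcome, a treatment coefficient in such a model is a difference in level between arms, averaged over months 0, 3, 6 and 12. At month 0 that difference has expectation zero because of randomisation. No treatment coefficient in this model is a between-arm difference in change.

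Two things follow if the model is fitted as worded. The coefficient is smaller than the 12-month effect the trial was sized for. And without treatment-by-time terms or baseline adjustment, the comparison carries the spread of breast size between participants and any chance baseline imbalance, which a change contrast largely removes. The risk is a false null on the main question.

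**Working it through.** **Inputs from the article.** Six groups of 15, so 45 v 45 for estradiol and 60 v 30 for any progesterone v none. Ratio of consecutive volumes 1.08, SD 0.27. Target increase 30%. Alpha 0.05. Stated power 0.95 (estradiol, A) and 0.94 (progesterone, B).

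**Assumptions, not in the article.** Two-sided test; difference 1.30 − 1.08 = 0.22 (the simulated difference is not stated); compound symmetry; complete data; the time courses and between-person SDs shown below.

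**Step 1: the stated power.** Power ≈ Φ(δ/SE − 1.96).

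- A: SE = 0.27·√(1/45 + 1/45) = 0.0569; 0.22/0.0569 = 3.87; power 0.972 (noncentral t, 84 df: 0.969).
- B: SE = 0.27·√(1/60 + 1/30) = 0.0604; 0.22/0.0604 = 3.64; power 0.954 (noncentral t: 0.950).

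The t-based figures are within two points of the stated ones. A difference of 0.30 gives more than 0.99 for both and does not fit. The sample size is therefore consistent with a comparison of change ratios.

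**Step 2: what the literal coefficient estimates.** In a balanced random-intercept model without treatment-by-time, the expected coefficient is (d0 + d3 + d6 + d12)/4, where d is the arm difference at each visit and d0 = 0.

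| Time course of the effect | Share of the 12-month effect | For a 22-point effect |
|---|---|---|
| Full from month 3 | (0 + 1 + 1 + 1)/4 = 75% | 16.5 |
| Linear growth | (0 + 0.25 + 0.5 + 1)/4 = 44% | 9.6 |
| Only at month 12 | (0 + 0 + 0 + 1)/4 = 25% | 5.5 |

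If d3 and d6 do not exceed d12, 75% is the ceiling. This step needs no SD and applies to either factor.

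**Step 3: precision, estradiol factor, log scale.**

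- Effect: ln(1.30/1.08) = 0.185.
- SD of log change: 0.27/1.08 = 0.25, and √ln(1 + 0.25²) = 0.246.
- Within-person SD: 0.246/√2 = 0.174.
- Literal coefficient: SE = √[(2/45)(σb² + 0.174²/4)], which is 0.066, 0.107 and 0.149 for between-person log SD σb = 0.3, 0.5 and 0.7.
- Simple change contrast: SE = 0.246·√(2/45) = 0.0519, whatever σb is.
- Month-12 contrast with a common baseline mean: SE = √[(2/45)(σb² + 0.174²)(1 − ρ²)], with ρ = σb²/(σb² + 0.174²).

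Power, both tails counted:

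| Analysis | σb = 0.3 | σb = 0.5 | σb = 0.7 |
|---|---|---|---|
| Literal model, linear growth | 0.23 | 0.12 | 0.08 |
| Literal model, full from month 3 | 0.56 | 0.26 | 0.15 |
| Simple 12-month change contrast | 0.95 | 0.95 | 0.95 |
| Month-12 contrast, common baseline mean | 0.97 | 0.96 | 0.95 |

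**Step 4: check on the ratio scale.** With a between-person SD of 30, 50 or 70% of mean volume and a 22-point effect, the literal model has power 0.31, 0.14 or 0.09 (linear) and 0.70, 0.34 or 0.20 (full from month 3), against 0.97 for the change contrast. Simulation of 150 trials per pattern at SD 50% gave mean literal coefficients of 9.5 (linear) and 16.9 (full from month 3), with power 0.12 and 0.35. With treatment-by-visit terms the month-12 contrast averaged 21.6 and 21.8, with power 0.96 and 0.99.

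**The case against.** The strongest reply is that the article gives no model formula, so an unwritten term is not an excluded one. The interaction sentence does not limit what the treatments interact with, and time has just been named as a determinant. Results are promised as mean change. The section also plans to stratify by treatment regimen, which with time in the model would give each regimen its own course from month 0 to month 12. An analysis plan that is not shown may contain the treatment-by-time terms.

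Much of this stands. A reader might infer that the trial will be analysed with the averaged coefficient and is therefore badly underpowered. The article does not support that: the wording leaves room for an analysis of change, and the power figures are conditional on the literal model and on assumed inputs. A reader might also infer that having month 0 among the outcome visits is itself a fault. It is not: a constrained longitudinal model keeps baseline in the outcome and estimates change properly.

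What does not stand is that this is only detail left for later. The article states the outcome, time points, treatment coding, interactions and the purpose of those interactions. That purpose concerns dose combinations, not change over time. What is written about the primary analysis does not yield the endpoint defined in the same article, and two analysts could fit materially different models from it.

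**Conclusion.** The point holds as a mismatch between the model as worded and the stated endpoint. Read literally, the treatment coefficients recover at most 75% of the 12-month effect provided earlier effects do not exceed it, and about 44% under linear growth. That attenuation depends only on the time course. The loss of power is less certain: about 0.08 to 0.56 for the estradiol factor on the log scale, against about 0.95 for a change contrast, and up to 0.70 against 0.97 in the ratio-scale check. It rests on a between-person SD and a time course that the article does not give, and on compound symmetry. Because a change analysis may well be intended, the severity is should-fix.

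**What to change.** State the primary model explicitly:

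- Visit as a categorical term, with estradiol × visit and progesterone × visit, in addition to whatever terms are kept for dose combinations.
- Adjustment for baseline volume in one of two ways: a common baseline mean across arms with month 0 kept in the outcome, or baseline volume as covariate with months 3, 6 and 12 as outcomes.
- The month-12 contrast of each factor as the primary estimate, with months 3 and 6 secondary.

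The visit interaction is needed under either option. Baseline adjustment alone would still average the three later visits, giving (0.25 + 0.5 + 1)/3 = 58% of the 12-month effect under linear growth.

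The cost is analysis wording only. The visits and measurements are already planned, and the text can be settled before the blinded analyst learns the treatment codes.

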### Characteristics of participants

Individuals who regularly visit the clinic are eligible to participate, provided that the individual started GAHT after 18 years of age (to eliminate potential effects of puberty suppression), received more than one year of GAHT, underwent vaginoplasty or orchiectomy (to avoid interference from androgen deprivation strategies), has sufficient knowledge of the Dutch language and a BMI 18–30 kg/m2. A potential subject who meets any of the following criteria will be excluded from participation in this study: previous use of progesterone/ progestin (not including cyproterone acetate or oral contraceptives), history of breast augmentation or reduction surgery, active treatment for depression, current use of progesterone/ progestin including cyproterone acetate, severe familial dyslipidemia (e.g. Familial Hypercholesterolemia), serum estradiol concentration > local reference range (200–400 pmol/L) at last visit prior to baseline, contraindications for the use of micronized progesterone, history of epilepsy (because of the oscillating 3D scanner).

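### Assessing weight change in 10 kg groups is too coarse for 90 participants over 12 months; a continuous term would serve this secondary analysis better

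*Protocol article*

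**What the plan says.** The Statistical analysis section of the protocol article describes a linear mixed model for breast volume with time, estradiol, progesterone and their interaction. It says the model can be adapted to look at effect modifiers, and then: "Analyses will be stratified to treatment regimen, age, weight change and serum hormone levels". The next sentence fixes the categories: "Age will be analyzed in quartiles and weight change will be assessed in 10 kg groups". Serum hormone levels are also to be split into quartiles. Weight change is thus the only one of these continuous factors given a fixed width, and no cut-points are stated.

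Weight is available as a measurement. Under Main study parameter/endpoints: "At baseline and during follow-up, the following patient characteristics will be recorded: age, height, weight, BMI". No continuous weight term is named anywhere. The one covariate list, which follows the satisfaction models, omits weight: "Treatment regimens, hormone levels and breast volume changes will be assessed as covariates".

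Two entry criteria under Characteristics of participants bear on how far weight is likely to move: "sufficient knowledge of the Dutch language and a BMI 18–30 kg/m2" and "received more than one year of GAHT".

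**The concern.** Quartiles of age or hormone level fill every stratum by construction, with about 22 of 90 participants in each. A fixed 10 kg width gives no such guarantee. In people within a limited BMI range and already established on hormones, most 12-month changes may be a few kilograms. The central bands would then hold nearly everyone and the outer bands almost no one.

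Two things follow. A stratum with no participants in some arms cannot supply the treatment estimates that stratification is meant to give. And within a band, someone at +1 kg is treated the same as someone at +9 kg, although both weights were recorded. What is at stake is the usefulness of a secondary analysis, not the main result.

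**Working it through.** **Inputs from the article.** 90 participants in six arms of 15; 12 months of follow-up; BMI 18–30; a clinically relevant volume increase of 30%; a ratio of consecutive volume measurements of 1.08 with SD 0.27.

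**Assumptions not in the article.** Normally distributed 12-month weight change with mean 0–2 kg and SD 3–8 kg; height 1.75 m; for step 4 only, 2% breast volume per kg.

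**1. The plan's own figures.** The article gives no figure for weight change. Its power figures (0.95 for estradiol, 0.94 for progesterone) do not depend on the weight analysis, but they give a yardstick. If the simulated contrast was 1.30 − 1.08 = 0.22 (not stated), power is about Φ(0.22 / [0.27 × √(1/n₁ + 1/n₂)] − 1.96). This gives 0.97 for 45 v 45 and 0.95 for 30 v 60, close to the stated values. So 22 percentage points is a fair reference for a planned effect.

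**2. Band width relative to the population.** At 1.75 m, BMI 18 is 18 × 1.75² = 55.1 kg and BMI 30 is 91.9 kg. A 10 kg band is 10/91.9 = 11% to 10/55.1 = 18% of body weight, or 10/1.75² = 3.3 BMI units out of an eligible range of 12.

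**3. Occupancy and information lost, mean +1 kg.** With p = P(change ≥ +10 kg), the expected number is 90p, and the chance that every arm has at least one such person is [1 − (1 − p)¹⁵]⁶. The last column is the within-band share of the variance in weight change, for bands cut at zero and for bands centred on zero.

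| SD (kg) | Within ±10 kg | Within ±5 kg | Expected at ≥ +10 kg, of 90 | All six arms have one | Variance lost, cut at 0 / centred |
|---|---|---|---|---|---|
| 3 | 99.9% | 89% | 0.1 | <0.01% | 38% / 56% |
| 4 | 98.5% | 78% | 1.1 | <0.01% | 32% / 36% |
| 5 | 95.0% | 67% | 3.2 | 0.6% | 25% / 25% |
| 6 | 90.0% | 59% | 6.0 | 7% | 19% / 19% |
| 8 | 78.5% | 47% | 11.7 | 45% | 12% / 12% |

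Over means of 0–2 kg, the two bands between −10 and +10 kg hold 94–100% at SD 3–5 and 78–90% at SD 6–8. A single band centred on zero holds 65–90% at SD 3–5.

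**4. How well bands adjust.** A large-sample simulation had no drug effect, arms differing by 1–3 kg in mean weight change, and SD 3–5 kg. Adjusting by 10 kg band left 20–55% of the weight-driven arm difference, which is 0.4–3.2 points. For a 2 kg difference, about 4 points unadjusted became 0.9–2.2 points with bands. A continuous term left about zero, as it must when the simulated relation is linear.

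**The case against.** The strongest reply is that little depends on this choice. The main comparison is randomised with a concurrent control, its model names no weight term, and weight change unrelated to treatment balances out on average. Band width cannot bias that estimate or lower its power. This stands, and it keeps the point minor.

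A reader might infer that the 10 kg groups make it impossible to separate breast growth from weight change, or that bands centred on zero show nothing. The figures do not support either reading. At SD 4–6 kg the bands still capture 64–81% of the variance in weight change, centred bands included, and they remove roughly 45–80% of a weight-driven arm difference. What remains is small beside 22 points.

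A reader might also take the weight analysis as the trial's control for confounding by weight. The article does not say so. It introduces the stratification directly after effect modification and lists weight change beside age and hormone levels.

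Requiring someone in all six arms is a strict test, because the article also analyses the two drugs separately and main effects pool arms. Pooling helps only a little: 1.1 to 6.0 people at or above +10 kg (SD 4–6) is 0.6 to 3.0 per estradiol level.

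The spread is assumed, and at SD 8 kg the sparsity argument weakens, although 11.7/6 is still only about two people per arm. Unstated cut-points may be settled in a fuller document and are not held against the article; the 10 kg width is stated.

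Finally, weight change arises after randomisation and the hormones may affect it. Conditioning on it in any form gives no clean treatment effect. This also stands, and it applies equally to the proposed fix.

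**Conclusion.** The point holds as a low-severity weakness in a secondary analysis. Fixed 10 kg groups are coarse for this population and duration. If the SD of weight change is about 3–5 kg, 94–100% of participants fall in two bands and the outer strata are too sparse for stratified treatment estimates; at SD 6–8 kg the share falls to 78–90%. The bands account for weight-related volume change only in part, discarding 19–36% of the variance in weight change at SD 4–6 kg and 38–56% at SD 3 kg (mean +1 kg). These sizes rest on an assumed normal distribution that the article does not supply, and the residual in volume points rests further on the assumed 2% per kg. The primary randomised comparison is untouched.

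**What to change.** In the secondary, effect-modifier analysis, replace the 10 kg groups with weight change in kg as a continuous term, calculated from the weights recorded at baseline and follow-up. Fit it as linear and check for curvature. If effect modification is of interest, add one treatment-by-weight-change term.

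Label the analysis exploratory and keep it out of the primary randomised comparison. State that weight change is measured after randomisation and may be affected by treatment, so a weight-conditioned estimate is not a clean treatment effect.

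The cost is a line or two of wording and no new data. The downside is an assumed shape for the relation between weight and volume, which the curvature check addresses.

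### Satisfaction, mood and sleep are made categorical although they are measured with multi-item scales, which costs power on secondary objectives

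*Protocol article*

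**What the plan says.** In the protocol article, Main study parameter/endpoints names the instruments. Satisfaction is assessed with "the Rosenberg self-esteem scale [21], the Breast Satisfaction Rating Scale (BSRS) and a non-validated satisfaction questionnaire about various aspects of the breasts". For the other two domains, "mood and sleep quality will be assessed using the Perceived stress scale, Inventory of Depressive Symptomatology, self-report (IDS-SR) and Pittsburgh Sleep Quality Index (PSQI) questionnaires". Sexual pleasure is assessed with the ASPI.

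The Statistical analysis section then sets the scale type: "Satisfaction, mood, sleep, and sexual desire will be recorded as categorical variables". The next sentence treats the remaining questionnaire differently: "Sexual pleasure will be assessed using a continuous scale of the ASPI score".

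On models, the same section says that "linear mixed model analyses with measurements clustered within participants will be performed, with breast volume as continuous outcome variable". For satisfaction it says "To analyze the relationship between satisfaction of different aspects of the breasts and breast volume, mixed model analyses will be performed", and adds "Treatment regimens, hormone levels and breast volume changes will be assessed as covariates". No model is named for mood or sleep.

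The last paragraph of Background lists satisfaction with breast volume, mood, sleep quality and sexual pleasure among the secondary objectives. Sexual desire is not among them. It appears in Background only as a literature finding, and no instrument for it is named.

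**The concern.** Two instruments that the article itself calls an index, the PSQI and the ASPI, receive opposite treatment, one categorical and one continuous, with no reason given. A change that moves a participant within a category but not across its boundary is lost to the analysis.

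Mood is where this matters most, because it is an objective and also bears on safety. Background reports mood swings as the most frequent side effect in an uncontrolled study of a progestin, and also raises a possible benefit of progesterone on mood and sleep. Characteristics of participants excludes people in active treatment for depression. If the categories were severity bands, few participants might cross a boundary, and a real shift in scores could be reported as no effect.

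**Working it through.** **1. The plan's own power figure.** Inputs from Statistical analysis: ratio 1.08, SD 0.27, target increase 30%, alpha 0.05 (taken as two-sided). I read the target as 1.30 against 1.08, so the difference is 0.22. With six groups of 15 and groups D, E and F on the doubled estradiol dose (Fig. 1), the margins are 45 v 45 for estradiol and 30 v 60 for no v any progesterone.

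- Estradiol: 0.22 / (0.27 × √(1/45 + 1/45)) = 3.865; Φ(3.865 − 1.96) = 0.972. With a noncentral t on 84 df: 0.969. Stated: 0.95.
- Progesterone: 0.22 / (0.27 × √(1/30 + 1/60)) = 3.644; Φ(3.644 − 1.96) = 0.954. With the t: 0.950. Stated: 0.94.

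The t-based values lie within 2 points of the stated ones, so the margins are a usable basis. This power is for breast volume. The article states none for satisfaction, mood or sleep.

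**2. Information kept after categorising.** For a normal score cut into k equal-probability categories with optimal scores, the fraction kept is k × Σ(φ(c_{j−1}) − φ(c_j))², where the c_j are the cut-points.

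- k = 2: 2 × 2 × 0.3989² = 2/π = 0.637
- k = 3: 3 × 2 × 0.3636² = 0.793
- k = 4: 4 × 2 × (0.3178² + 0.0812²) = 0.861

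**3. Power at an assumed effect of 0.6 SD, 45 v 45.**

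- Continuous: 0.6 / √(2/45) = 2.846; Φ(2.846 − 1.96) = 0.81.
- Two categories, split midway between the group means: p1 = 0.382, p2 = 0.618, difference 0.236. Then (0.2358 × √45 − 1.96 × √0.5) / √0.4722 = 0.285; Φ(0.285) = 0.61.

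For 30 v 60 the same calculation gives 0.77 and 0.56.

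**4. More than two ordered categories.** Simulation with 3,000 runs: t test on the score, rank test on the categories, cut-points centred midway between the group means. Simulation error is at most about 0.9 point (√(0.25/3000)).

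| Comparison | Effect (SD) | Continuous | Four | Three | Two |
|---|---|---|---|---|---|
| 45 v 45 | 0.5 | 0.657 | 0.601 | 0.558 | 0.458 |
| 45 v 45 | 0.6 | 0.801 | 0.749 | 0.714 | 0.608 |
| 45 v 45 | 0.7 | 0.910 | 0.867 | 0.845 | 0.736 |
| 30 v 60 | 0.5 | 0.586 | 0.524 | 0.494 | 0.413 |
| 30 v 60 | 0.6 | 0.761 | 0.689 | 0.661 | 0.568 |
| 30 v 60 | 0.7 | 0.870 | 0.813 | 0.790 | 0.695 |

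Three or four categories cost about 4 to 10 points. By the formulas in step 3, two categories cost about 17 to 20 points over the same effects.

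**5. An off-centre cut-off.** If only 10% of the reference group lies beyond a single cut-off, power at 0.6 SD is 0.46 for 45 v 45 and 0.37 for 30 v 60.

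**The case against.** The strongest reply is that the sentence says recorded, not dichotomised or analysed in groups. Satisfaction is asked about single aspects such as symmetry, volume and nipple shape, partly with a non-validated questionnaire, and ordered answers are natural there. Category definitions and models for secondary scales are also commonly left to the full protocol or SAP, which are not shown. The first part stands for single items. It fits poorly with the IDS-SR, the PSQI and the Perceived stress scale. The second part stands as to missing detail, so the absent cut-points are not the fault. The fault is the stated rule, which an SAP following the article would carry forward.

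A reader might infer more than the text supports:

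- **That a linear mixed model is misapplied to a categorical outcome.** The article uses the word linear only for breast volume. The satisfaction analysis is called a mixed model, which could be ordinal or logistic, and mood and sleep have no named model.
- **That 90 participants are reduced to about 57 (90 × 0.637).** The arithmetic is right, but it belongs to a median split of a normal score, which the article never mentions.
- **That comparisons rest on 15 per group.** That holds for contrasts between single groups. The main effects use the margins of 45 v 45 and 30 v 60.
- **That harms would go unseen.** Adverse effects are recorded separately and compared with Fisher's exact test.

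**Conclusion.** The point holds as a weakness in the analysis of secondary outcomes. The article fixes a categorical scale type for domains measured with multi-item scales, keeps a comparable instrument continuous, and gives no reason. Following that rule loses power on satisfaction, mood and sleep.

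The size cannot be fixed from the article. It is modest with three or four ordered categories analysed as ordered, and large with a two-way split or an off-centre cut-off. The figures assume a normal score, effects of 0.5 to 0.7 SD (the article gives none for these scales), complete data on 90 participants and a single time point. They also assume that each named scale yields a total score, which its description as a scale, inventory or index suggests but the article does not spell out.

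Sexual desire without an instrument is a separate, minor inconsistency. The primary conclusion on breast volume is unaffected.

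**What to change.** In Statistical analysis, replace the sentence on categorical variables with the following:

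- The total scores of the Rosenberg scale, BSRS, Perceived stress scale, IDS-SR and PSQI are analysed as continuous outcomes, as the ASPI score already is, in a mixed model with the factorial treatment terms and visit. Effects are reported with 95% confidence intervals.
- Published cut-offs, where the team wants them, are used for description only.
- Single-item satisfaction questions are analysed with an ordinal mixed model.

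If categories are to be kept for a total score, define them and name a matching ordinal or logistic mixed model before the data are analysed.

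Reconcile sexual desire with Background and Main study parameter/endpoints, which name only sexual pleasure as an outcome: name its instrument or delete the term.

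The cost is wording, provided that item answers or total scores are stored. The questionnaires are already part of the study, so no visit, participant or measurement is added.
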